# Effects of double vs triple injection on block dynamics for ultrasound-guided intertruncal approach to the supraclavicular brachial plexus block in patients undergoing upper limb arteriovenous access surgery: study protocol for a double-blinded, randomized controlled trial

**DOI:** 10.1186/s13063-022-06260-6

**Published:** 2022-04-12

**Keywords:** Intertruncal approach, Ultrasound, Brachial plexus, Supraclavicular block, Injection technique

## Abstract

**Background:**

Ultrasound-guided intertruncal approach (IA) has been proposed to be an alternative and promising approach to the supraclavicular block (SCB), in which double injection (DI) of local anesthetics (LA) is sequentially administered between intertruncal planes. We would like to apply a refined injection technique, named triple injection (TI) technique, based on the 3 separate compartments visualized by ultrasound. The aim of this study is to compare the percentage of patients with complete sensory blockade at 20 min of DI vs TI technique, when they are applied in patients undergoing upper limb arteriovenous access surgery.

**Methods:**

This study is a prospective parallel-group randomized controlled trial. A total of 86 end-stage renal disease patients will be randomly allocated to receive IA-SCB using either DI or TI technique with identical LA (0.5% ropivacaine 24 mL). The primary outcome is the percentage of patients with complete sensory blockade of all 4 terminal nerves (median, ulnar, radial, and musculocutaneous nerves) of the brachial plexus measured at 20 min after injection. The secondary outcomes will consist of the sensory or motor blockade of all individual nerves, onset times, performance time, diaphragmatic paralysis, surgical anesthesia, and adverse events.

**Discussion:**

It is expected that ultrasound-guided IA-SCB with the TI technique results in better block dynamic in patients undergoing upper limb arteriovenous access surgery.

**Trial registration:**

Chinese Clinical Trial Registry ChiCTR2100045075.

## Introduction

Supraclavicular block is the most common and preferred anesthesia method for arteriovenous (AV) fistula formation surgery [1]. Since nerve blocks tend to increase vasodilation, blood flow, and tissue oxygenation during autogenous AV fistula creation, they improve the successful rate of fistula [2]. Furthermore, supraclavicular block anesthetizes the brachial plexus at the level of the first rib, where all trunks and divisions are in their most compact form, thus providing a complete and reliable block for upper extremity surgery [3]. Although various ultrasound-guided needle techniques to supraclavicular block have been reported to have satisfying success rate and onset times, these techniques have been associated with an incomplete blockade for the ulnar nerve innervated area and a high risk of intraneural injection, respectively [3, 4]. The intertruncal approach to the supraclavicular brachial plexus (IA-SCB) was first described by Siddiqui et al. [5] in 2020, in which the needle tip targets the two intertruncal tissue planes between the 3 trunks. In authors’ experience, this new approach results in rapid and consistent blocking of all terminal nerves of the brachial plexus. Compared with the sub-epineurium techniques to the supraclavicular block, its superiority is to provide complete sensory-motor blockade of the entire brachial plexus while avoiding intraneural injection and pleural puncture on anatomy.

However, the biggest challenge of targeting two intertruncal planes is that we do not know exactly where our needle tip lies between the two planes. It may lie in an incorrect location, even as we see the needle tip in place on ultrasound imaging. Because the homogeneous fascia tightly compresses together, it does not allow for easy identification of these elements as separate structures [5]. Incorrect injection probably results in an atypical diffusion pattern of LA and following incomplete block. In clinical practice, we observe that the 3 trunks can be separated by clear edges rather than being a singular cluster, the outer boundaries (epineurium) of each trunk allow injection of LA into the 3 separate compartments under real-time ultrasound guidance. Therefore, we refined the needle technique by depositing LA inside the 3 trunks separately (named triple injection, TI) with clear identification of the epineurium of each trunk, that is the needle tip will be accurately pierced into the epineurium in a “bottom to top” manner.

Needle techniques for traditional supraclavicular blocks include sub-epineurium injection (e.g., double injection [6]), intracluster injection (e.g., triple [7], targeted intracluster injection [8, 9]), or extra-epineurium injection (e.g., corner pocket injection [10]). Although the total anesthesia-related times vary in those studies, the results have demonstrated that the multiple injection technique is feasible and can achieve faster onset times and higher success rates within 30 min after injection, with no increase in complications [11]. The triple-injection technique described by Arab et al. [7] was designed based on the clusters of the brachial plexus at the level of the first rib, which can be artificially divided into three parts. The percentage of patients with complete sensory blockade was up to 76% in TI vs 56% in single injection for upper limb arteriovenous access surgery at 20 min after injection. However, a cadaver study has reported that even single intracluster injection could lead to a high risk of sub-perineurium injections (up to 24%) in the traditional supraclavicular block, which raised concerns about nerve injury [4]. Fortunately, the 3 separate compartments visualized during the intertruncal approach are naturally occurring along the trajectory of the brachial plexus, in which each trunk is separated not yet blended. Consequently, in this trial, we will compare DI vs TI ultrasound-guided IA-SCB. Based on our initial experience, we hypothesized that the new TI technique will result in a higher percentage of patients with complete sensory blockade in the first 20 min, while avoiding puncture-related adverse events.

## Methods and analysis

### Trial design

This study is a single-center, randomized, double-blind, parallel-group clinical trial with concealed 1:1 allocation to receive either a DI or TI technique to IA-SCB of patients scheduled for elective upper limb arteriovenous access surgery. The trial will be carried out at the Guangdong Provincial People’s Hospital, Guangzhou, Guangdong, China, and started in July 2021 and the recruiting period will be 18 months. Trial methods and results will be reported according to the Consolidated Standards of Reporting Trials (CONSORT) 2010 guidelines (Fig. 1). The schedule of enrolment and assessments is shown in the Standard Protocol Items: Recommendations for Interventional Trials (Fig. 2).

**Fig. 1 Fig1:**
[figure not shown]
Flow diagram of this study according to Consolidated Standards of Reporting Trials (CONSORT) 2010 guidelines. IA, intertruncal approach; SCB, supraclavicular block; DI, double injection; TI, triple injection

**Fig. 2 Fig2:**
[figure not shown]
Standard Protocol Items: Recommendations for Interventional Trials. IA, intertruncal approach; SCB, supraclavicular block; DI, double injection; TI, triple injection

### Participant eligibility and consent

The investigators involved in this trial will identify consecutive eligible patients according to the listed criteria. The benefits, risks, and data privacy of this study will be explained in detail during the preoperative visit 1 day before surgery. Written informed consent will be obtained from each patient before enrollment. This study is voluntary, and the participants are free to withdraw from the study at any time.

### Inclusion criteria

Having signed the written informed consentAmerican Society of Anesthesiologists (ASA) physical status < IVAged 18–75 yearsPatients scheduled for creation or superficialization of arteriovenous fistula or aneurysmectomy or arteriovenous fistula with artificial vessels for renal dialysis

### Exclusion criteria

Patient’s refusal to brachial plexus blockCoagulopathy: INR ≥ 1.4, or PLT < 100 × 10^9^/L, or APTT ≥ 40s, or PT ≥ 17 sPre-existing neuropathyInfection at the supraclavicular fossaHypersensitivity or allergy to LASevere pulmonary disease or poor respiratory reserve: patients require home oxygen therapy or non-invasive ventilation, or limit exercise tolerance to < 4 METs (maximum exercise tolerance)Severe hepatic insufficiency: Child-Turcotte-Pugh score > 9Severe cardiac insufficiency: cardiac conditions that limit exercise tolerance to < 4 METs or left ventricular ejection fraction (LVEF) < 40%Severe mental illness or cognitive dysfunctionBody mass index (BMI) > 35 kg/m^2^Pregnancy or breastfeeding womenUrgent surgery

### Dropout criteria

Patients voluntarily withdraw from the studyChange of operation or anesthesia methods before or during surgeryPatients do not cooperate with postoperative follow-upNot implemented according to the study plan

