### Outcome measures

#### Primary outcome measure

The primary outcome will be the percentage of patients with complete sensory blockade of all 4 terminal nerves (median, ulnar, radial, and musculocutaneous nerves) of the brachial plexus measured at 20 min after injection. The sensory blockade will be evaluated using a validated 3-point scale (0 = no block, the patient has normal sensation; 1 = partial anesthesia, the sensation is reduced compared with the contralateral limb; and 2 = complete anesthesia) by an outcome evaluator (either anesthesiologist or anesthesia nurse). Sensory blockade of the musculocutaneous, median, radial, and ulnar nerves will be evaluated on the lateral aspect of the forearm, the volar aspect of the thumb, the lateral aspect of the dorsum of the hand, and the volar aspect of the fifth finger, respectively. The complete sensory for each innervated nerve was defined as score is equal to 2 points. We will consider the patients having a complete sensory blockade when a minimal composite score of 7 points is achieved.

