#### Secondary outcome measures

The onset time is defined as when a minimal composite sensory-motor score of 14 points is achieved. The assessment of sensory-motor blockade will be performed every 5 min until 30 min after injection. The above 3-point scale is used for evaluating sensory blockade, and another similar 3-point scale (0 = no block, 1 = paresis, 2 = paralysis) for motor blockade. Motor blockade of the musculocutaneous, radial, median, and ulnar nerves will be evaluated by elbow flexion, thumb abduction, thumb opposition, and thumb adduction, respectively.The performance time (including imaging time and needle time) is defined as the time interval between contact of the ultrasound probe with the skin and complete injection of LA.The incidence of diaphragmatic paralysis measured with M-mode as described by Boussuges et al. [13] at 35 min after injection.Successful surgical anesthesia is defined as one with adequate surgical block without complaining pain during simulated surgical stimulus (forceps pinching the prospective surgical area) at 30 min after injection.Operation-related adverse events include puncture-related paresthesia, procedural-related pain, Horner syndrome, vascular puncture, pneumothorax, toxicity of LA, or neurological deficits. The puncture-related paresthesia will be recorded by self-report during performing nerve block, and the procedural-related pain is assessed by the numeric rating scale (0 = no pain, 10 = worst possible pain). Horner syndrome, vascular puncture, pneumothorax, and toxicity of LA will be recorded as the incidence in each group. All patients will be followed up for 72 h after surgery for suspicious symptoms of nerve injury such as paresthesia or motor deficit.

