### Sample size calculation

Sample size is calculated according to the study of Arab and colleagues [7]. In clinical practice, multipoint injection and satisfactory diffusion of LA will result in more complete sensory or motor blockade and faster onset times. Therefore, we expected a higher rate of complete sensory blockade using the new TI technique. Based on a pilot study (15 patients), the rate was 66.7% (patients with complete sensory blockade) at 20 min after injection, when patients received a standardized IA-SCB with the DI technique. We hypothesized that the TI technique will be capable of increasing this rate to 90%; with a statistical power of 0.80 and a *α* level of 0.05, the required sample size is calculated to 36 patients per group. A total of 43 patients per group will be required to account non-included patients (15% dropout rate).

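### The dropout criteria, read with the sample size section, would remove randomised patients for events after randomisation, some possibly tied to block failure, although the 20-min primary outcome is normally already recorded

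*Protocol article*

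**What the plan says.** Four statements in the protocol article bear on this.

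- **Dropout criteria.** Besides voluntary withdrawal, the list covers a change of "operation or anesthesia methods before or during surgeryPatients do not cooperate with postoperative follow-upNot implemented according to the study plan" (three list items run together in the extracted text). No exception is made for a change of anaesthesia caused by an inadequate block, and departure from the plan is not defined.
- **Sample size calculation.** "A total of 43 patients per group will be required to account non-included patients (15% dropout rate"). Dropouts are thus equated with patients who are not included.
- **Primary outcome measure.** The endpoint is "complete sensory blockade of all 4 terminal nerves (median, ulnar, radial, and musculocutaneous nerves) of the brachial plexus measured at 20 min after injection".
- **Secondary outcome measures.** "Successful surgical anesthesia is defined as one with adequate surgical block without complaining pain during simulated surgical stimulus", tested at 30 min. Nerve-injury follow-up runs to 72 h after surgery.

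Under Allocation and blinding, the envelope is opened on the day of surgery and the block is then given according to allocation. Patients, the outcome evaluator and follow-up staff are blinded; the operators cannot be. The Statistical plan section names no analysis set and does not bring dropouts back in.

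**The concern.** Three features together make the rule unsafe.

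1. **Timing.** A change of anaesthesia during surgery, or poor cooperation after it, comes later than the 20-min score. Dropping such a patient discards an observed primary outcome; nothing is missing.
2. **Link to outcome.** A block that does not work is one plausible reason to change the anaesthetic. If such patients are dropped, selection is on something close to the primary endpoint, and the same patients leave the surgical anaesthesia outcome.
3. **Discretion.** The criterion on departure from the plan has no definition and no named judge. Operators who know the allocation may be the ones to apply it, so removal could differ between arms.

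At stake is the randomised comparison itself. Equal removal of failures inflates both rates and shrinks the difference. Unequal removal can create a difference where there is none.

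**Working it through.** **The plan's own figure.** 36 / (1 − 0.15) = 42.35, rounded up to 43 per group, 86 in total. The inflation reproduces, and it confirms that dropouts are expected to be absent from the 36 who count. How 36 itself was obtained is a separate matter and is not used here.

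**Inputs from the documents.**
- DI rate: "Based on a pilot study (15 patients), the rate was 66.7"%.
- TI rate: "We hypothesized that the TI technique will be capable of increasing this rate to 90"%.
- 43 per arm, 15% dropout, α 0.05.

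**Assumptions.** f is the share of 20-min failures later removed as dropouts. The documents give no value. The test is taken as two-sided; the protocol does not state the sidedness.

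**Plausible range for f.** The allowance is 0.15 × 43 = 6.45 patients per arm. Expected 20-min failures are 43 × 0.333 = 14.3 in DI and 43 × 0.10 = 4.3 in TI. Removing 40% of DI failures takes 0.40 × 14.3 = 5.7 patients, within the allowance. Removing 50% takes 7.2, above it. The range is therefore kept to 10% to 40%.

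**Rate seen after removal.** p / [p + (1 − p)(1 − f)]. For f = 0.40:
- DI: 0.667 / (0.667 + 0.333 × 0.60) = 0.667 / 0.8668 = 0.770
- TI: 0.90 / (0.90 + 0.10 × 0.60) = 0.90 / 0.96 = 0.938

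**Same f in both arms, true rates 66.7% and 90%.** Power is simulated with 43 randomised per arm and a two-sided 0.05 test of two proportions.

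| f | DI seen | TI seen | Difference (points) | Power |
|---|---|---|---|---|
| 0 | 66.7% | 90.0% | 23.3 | 0.78 |
| 10% | 69.0% | 90.9% | 21.9 | 0.74 |
| 25% | 72.8% | 92.3% | 19.6 | 0.67 |
| 40% | 77.0% | 93.8% | 16.8 | 0.59 |

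**No true effect (66.7% in both arms), failures removed in one arm only.**

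| f in that arm | False difference (points) | Two-sided type I error |
|---|---|---|
| 0 | 0 | 0.05 |
| 10% | 2.3 | about 0.06 |
| 25% | 6.1 | 0.09 |
| 40% | 10.3 | 0.17 |

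With no true effect and the same f in both arms, type I error stays near 0.05. The false-positive risk comes only from unequal removal, and it favours whichever arm loses its failures.

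**The case against.** **Exclusion is inferred.** A reader might take the protocol to say outright that block failures leave the primary comparison. It does not. The dropout list gives no analysis consequence, and analysis sets are often left to an analysis plan, which is not shown here. This limits how firmly the point can be put. It does not remove it: the protocol does list these reasons, and it does size the trial as though the patients concerned are not included.

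**Block failure is kept as an outcome.** Surgical anaesthesia is tested at 30 min, before surgery, and compared between groups. That makes sense only if inadequate blocks stay in the data. This favours a benign reading, but the dropout list has no exception that would secure it.

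**A 20-min failure is not a conversion.** Scoring continues to 30 min, so a block incomplete at 20 min may be adequate for surgery. This stands. Every value of f is an assumption, and at f = 10% the harm is small.

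**Direction.** A reader might infer that TI, with three targets, is harder to complete, so that its failures would be removed preferentially and TI favoured. The documents do not support this. The Introduction calls locating the needle tip between the two DI planes the main difficulty and presents the TI targets as clearly identifiable. Operators must have made over 60 attempts with each technique. If removal is equal, the bias works against TI.

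**Larger figures.** Removing half of all failures would give power of about 0.52, or type I error of about 0.26 if in one arm only. In an arm with the 66.7% rate that takes 7.2 patients, more than the whole allowance, so these figures should not be relied on.

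**Conclusion.** The point holds as a fault in stated text. Following the dropout list together with the sample size section would remove randomised patients for events after randomisation, partly for reasons that may be linked to a failed block, and mostly after the primary outcome has been read.

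The size and direction of any bias are unknown. Within the protocol's own allowance, the effect runs from slight (a loss of 1.4 points in the difference and 0.04 in power at f = 10%) to material (a loss of 6.5 points and 0.19 in power at f = 40%). If removal falls on one arm only, type I error reaches about 0.17 at f = 40%. These figures assume that every removed patient counted here is a 20-min failure and that the planning rates are true. They show what the rule permits and are not a forecast.

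**What to change.** Amend the Dropout criteria and Statistical plan sections to say:

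- The listed reasons end trial procedures or follow-up. They do not remove a patient from the primary analysis.
- The primary analysis includes all randomised patients who received a block attempt, in the assigned group, using the recorded 20-min score whatever happens later.
- Patients in whom the allocated technique could not be completed, or whose anaesthesia was changed for an inadequate block before 20 min, count as not having complete sensory blockade.
- The 30-min surgical anaesthesia result is kept for patients whose anaesthesia is changed later.
- A per-protocol analysis is a sensitivity analysis only, with departure from the plan defined beforehand.

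This needs no new data and no extra patients. The cost is procedural. The Trial status section says that patients have already taken part, and the Protocol amendments section in principle allows changes only for safety and requires Institutional Review Board approval. The change should be approved, dated and recorded before any unblinded analysis.

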### Allocation and blinding

Sequence generation: Randomization will be performed based on 9 permuted blocks with block sizes of 10 for covering the total sample size. This will be done using computer-generated random numbers (Randomization.com).Allocation concealment mechanism: The investigator ([name] and [name]) will be responsible for patient recruitment. Randomization will be done by a settled research assistant during the study period. A sealed opaque envelope containing a card with a randomization number generated by a computer will be opened on the day of surgery.Implementation: The nerve block will be carried out by one of the five investigators ([name], [name], [name], [name], and [name]) according to treatment allocation, who all have extensive experience with both techniques (over 60 attempts/per technique) before the studyBlinding (masking): Outcome assessments will be conducted by one blinded anesthesiologist of assessment staff who will not communicate with the nerve block operators. During the study period, patients, outcome evaluator, and follow-up personnel (two research assistants) will be kept blinded to the group allocation. If block-related serious adverse events (e.g., pneumothorax or LA systemic toxicity) occur during or after the nerve block procedure, un-blinding will be permissible, and the corresponding treatment measures will be initiated under the supervision of the chief investigators ([name] and [name]).

### Interventions

All the enrolled patients will be randomly allocated to one of the following two study groups:
Control group: patients will receive a standardized IA-SCB using the DI technique.Experimental group: patients will receive a modified IA-SCB using the TI technique.

### Ultrasound-guided nerve block techniques

Before starting the study, all included patients will be instructed on the use of a validated 3-point scale for evaluating sensory-motor blockade. None of the patients will receive premedication. Standard ASA monitoring, including non-invasive cuff blood pressure, pulse oximetry, and 5-lead electrocardiogram, will be applied in the operating room. An intravenous access (18- or 20-gauge) will be established in the contralateral forearm, and the premedication (midazolam 1–3 mg and fentanyl 0.5 μg/kg) will be administered as anxiolytic. Supplemental oxygen (total flow, 4 L/min) will be given via nasal cannula during nerve block and surgery. For ultrasound-guided IA-SCB, the nerve block will be performed with ultrasound (Philips CX50) and high-frequency (3–12 MHz) linear array probe and 80-mm short-beveled stimulating needle (B. Braun Melsungen AG, Melsungen, Germany) following standard skin disinfection.

The DI technique will be performed according to the method described by Siddiqui et al. [5], and an optimal order of injections will follow the suggestion in Endersby’s Letter [12]. The probe is initially placed in the supraclavicular fossa and then moves towards the base of the neck in a coronal oblique plane. To obtain a satisfactory image, the probe will be adjusted with a slight posterior tilt and moved side to side. The 3 trunks (upper, middle, and lower) with individual outer boundaries (epineurium) are clearly identified in the short axis. In this area, all 3 trunks are displayed as three fascial compartments lateral to the subclavian artery, in which the upper trunk is the most superficial, the lower trunk is located above the first rib, and the middle trunk is just sandwiched between two trunks (Fig. 3A, B). After obtaining a satisfactory image, we used a pre-injection technique with 3 mL of LA for the superior identification of epineurium before administering the first LA dose. For the DI technique, the operators initially orientate the needle tip to the lower intertruncal tissue plane (between the middle and lower trunks), and a total of 12 mL of 0.5% ropivacaine (Astrazeneca Pharmaceutical Co., Ltd.) will be injected. If the first 1–2 mL LA does not demonstrate optimal spread between two planes, the needle tip will be repositioned slightly in “advance or retreat” manners until the desired spread pattern of LA is visualized. Subsequently, the needle withdraws and targets the upper intertruncal tissue plane (between the upper and middle trunks) (Fig. 3C). The remaining volume (12 mL) will be carefully injected incrementally into that plane. For the TI technique, once a satisfactory image is obtained, the operators accurately orientated the needle tip into the epineurium of the 3 trunks in a “bottom to top” manner using an in-plane technique. That is, LA is injected in 3 aliquots of 8 mL each. Aliquots will be deposited sub-epineurium around the upper, middle, and lower trunks respectively (Fig. 3D).

